### Statistical analysis

All baseline continuous variables between groups will be compared using general linear modelling, whilst categorical variables will be compared using exact logistic regression. The rates of change will be estimated for each patient separately by linear regression. General linear modelling, will be used to compare the mean rate of change in primary outcome measures between groups, unadjusted and adjusted for actual and potential confounding variables. Mean differences, 95% confidence intervals and P-values will be corrected for repeated measures, and P-values corrected for multiple comparisons by the Holm method. All analyses will be performed using Stata/IC 10.1 for Windows (StataCorp LP, College Station, Tx).

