**Method and Design:**

This is a randomised, placebo controlled clinical trial. A total of 66 renal transplant recipients will be enrolled and allocated to receive either 12 mg/day of astaxanthin or an identical placebo for one-year. Patients will be stratified into four groups according to the type of immunosuppressant therapy they receive: 1) cyclosporine, 2) sirolimus, 3) tacrolimus or 4) prednisolone+/-azathioprine, mycophenolate mofetil or mycophenolate sodium. Primary outcome measures will be changes in 1) arterial stiffness measured by aortic pulse wave velocity (PWV), 2) oxidative stress assessed by plasma isoprostanes and 3) inflammation by plasma pentraxin 3. Secondary outcomes will include changes in vascular function assessed using the brachial artery reactivity (BAR) technique, carotid artery intimal medial thickness (CIMT), augmentation index (AIx), left ventricular afterload and additional measures of oxidative stress and inflammation. Patients will undergo these measures at baseline, six and 12 months.

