### Randomization

The clinical trial pharmacist at the Launceston General Hospital or Royal Brisbane and Women's, who is independent of the study team, will perform the randomization. Subjects will also be stratified according to four groups according to the type of immunosuppression used for the renal transplant. The four groups will be those taking 1) cyclosporine, 2) tacrolimus, 3) sirolimus and 4) prednisolone together with either azathioprine, mycophenolate mofetil or mycophenolate sodium. Computer generated random numbers will be placed in blocks of ten by the clinical trial pharmacist and related to a series of drug code numbers. Each drug code assignment block will refer to one of the stratification groups. Data recorded will include the drug code number, which becomes the subjects Xanthin trial identification number, the patient hospital record number, the date of allocation, and the type of immunosuppressant used. The sheet containing the blocks of drug code numbers are given to the clinical trial coordinator who thus is blinded to the allocation performed by the pharmacist. Once the immunosuppressant type is confirmed by the principal investigator the clinical trial pharmacist selects the next available drug code number from the relevant stratification block according to the type of immunosuppressant. This enables the pharmacist at the patient's location to dispense from the appropriate randomization group. The subject receives a specific purpose numbered Xanthin trial plastic container with tablets enclosed, which are indistinguishable as to whether they contain astaxanthin or placebo. The randomization code is kept sealed in an opaque envelope in the Launceston General Hospital and an identical copy is kept at an off-site location of one of the associate investigators for the duration of the study.

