### Power calculation

Resource limitations will allow us to recruit 66 patients within a two-year period. Data from other studies indicates that Pentraxin 3 has the highest variability of the three outcome measures (mean ± SD; isoprostanes = 54.1 ± 7.0 [46], PWV = 11.4 ± 2.4 [47], pentraxin 3 = 0.75 ± 0.3 [48]). We assume that a decrease of 10% in pentraxin 3 would be clinically significant. Therefore, with alpha = 0.05, we will have about a 17% power to detect this 10% change in pentraxin 3 and a 52% power to detect a 20% change. This also allows for a 20% withdrawal rate. We recognize that the power of the study is small, but believe that the study will form the basis for progression to a larger study.

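### Each primary outcome is analysed both unadjusted and adjusted with neither ranked first, the stratification factor is not named as a covariate, and randomised groups are compared at baseline by model

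*Protocol article*

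**What the plan says.** The Statistical analysis section of the protocol article makes three statements that bear on this point.

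- On baseline: "All baseline continuous variables between groups will be compared using general linear modelling, whilst categorical variables will be compared using exact logistic regression".
- On the primary outcomes, general linear modelling will "compare the mean rate of change in primary outcome measures between groups, unadjusted and adjusted for actual and potential confounding variables". No covariate is listed and neither version is called primary.
- On multiplicity: "P-values corrected for multiple comparisons by the Holm method". The set of P-values that the correction covers is not defined.

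There are three primary outcomes: aortic pulse wave velocity, plasma isoprostanes and plasma pentraxin 3. The Randomization section adds: "Subjects will also be stratified according to four groups according to the type of immunosuppression used for the renal transplant". The Statistical analysis section does not mention that factor.

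**The concern.** Three features of the plan work against a clean answer.

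First, the baseline comparison. Allocation is by computer-generated random numbers, so if it was carried out soundly every baseline null hypothesis is true. A test can then return only chance findings, and it says nothing about which variables predict outcome.

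Second, two results per primary outcome. Three hypotheses yield six P-values, and where the two versions disagree the plan gives no rule for which one answers the question.

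Third, the basis for adjustment. In a randomised comparison, covariates earn their place by predicting the outcome or by having been used in the randomisation, not by being confounders. The wording leaves room to choose covariates after imbalance has been seen, while the one factor that the design itself supplies goes unnamed.

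At stake are the error rate of the primary claims, and a clear estimate of effect from a trial whose stated purpose is to lead to a larger one.

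**Working it through.** **Inputs from the article.** Three primary outcomes; alpha 0.05; 66 patients ("Resource limitations will allow us to recruit 66 patients within a two-year period"); pentraxin 3 mean 0.75, SD 0.3; stated power 17% for a 10% change (0.075) and 52% for a 20% change (0.15).

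**Assumptions.** Two-sided tests and 33 per arm, since the article gives neither sidedness nor allocation ratio. *Groups* in the analysis section means treatment arms, although the article also uses the word for the strata. The three outcomes are independent. The covariates explain a share R² of outcome variance of 10%, 25% or 40%; the article gives no figure.

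**The plan's own figure.** Power = Φ(δ / (SD·√(2/n)) − 1.96). With n = 33, SD·√(2/n) = 0.3 × √(2/33) = 0.0739.
- δ = 0.075: Φ(1.016 − 1.960) = 17.2%
- δ = 0.15: Φ(2.031 − 1.960) = 52.8%

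The noncentral t gives 17.0% and 51.6%. The stated powers therefore reproduce for a single test at 0.05 with all 66 patients analysed. Whether they also allow for withdrawal is a separate matter.

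**Baseline comparisons.** With k independent variables, the chance of at least one P < 0.05 under sound randomisation is 1 − 0.95^k: 23% for k = 5, 40% for k = 10, 64% for k = 20. These counts are assumed.

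**Two versions per outcome.** Under the null, the unadjusted and the fixed-covariate adjusted z statistics are approximately bivariate normal with correlation √(1 − R²), which is 0.949, 0.866 and 0.775. Let e(a) be the probability that at least one of the two is significant at two-sided level a. If either version may count, family-wise error for three independent outcomes is 1 − (1 − e(a))³. The level a is 0.05/3 if Holm covers three outcomes and 0.05/6 if it covers six P-values, because under the global null an error requires a rejection at Holm's first step.

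| R² | e(0.05), one outcome, no Holm | Family-wise error, Holm over three | Family-wise error, Holm over six |
|---|---|---|---|
| 10% | 6.5% | 1 − (1 − 0.0224)³ = 6.6% | 1 − (1 − 0.0114)³ = 3.4% |
| 25% | 7.3% | 1 − (1 − 0.0256)³ = 7.5% | 1 − (1 − 0.0131)³ = 3.9% |
| 40% | 8.0% | 1 − (1 − 0.0278)³ = 8.1% | 1 − (1 − 0.0142)³ = 4.2% |

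With one P-value per outcome and Holm over three, the same formula gives 1 − (1 − 0.05/3)³ = 4.9%. A separate null simulation (52 patients analysed, 5 or 10 covariates explaining 10% to 50% of variance) put the per-outcome either-counts error at 6.8% to 8.6%, in line with the second column.

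**Price of a six-member family.** For a single unadjusted test of a 20% change in pentraxin 3 with 33 per arm, the strictest Holm step gives:
- level 0.05/3: Φ(2.031 − 2.394) = 36%
- level 0.05/6: Φ(2.031 − 2.638) = 27%

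These are first-step figures; later Holm steps are less strict.

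**If covariates were chosen by observed imbalance.** Null simulations with assumed covariate counts (5 to 20) and selection at P < 0.05 or P < 0.10 put the adjusted test's own level at roughly 2% to 5%, and the either-counts error at about 5.4% to 6.4% per outcome. That route mainly makes the adjusted test conservative and adds little inflation.

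**The case against.** A reader might infer that covariates will be picked from the data, taking *actual* confounders to mean variables found to differ between the arms. The text does not support that. It states no link from the baseline comparisons to covariate choice and gives no selection rule. *Actual* is paired with *potential* and may simply mean known as opposed to suspected confounders. The most that can be said is that the wording does not exclude such selection.

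A reader might also infer that the error rate is certainly inflated. That is not established either. The plan does state a Holm correction and does not limit it to three P-values. If all six are in the family, error is controlled. Nor does the article say that success on either version would be claimed.

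It is also fair to say that reporting both unadjusted and adjusted estimates is ordinary practice, that a condensed article commonly leaves the covariate list to a fuller plan, and that baseline P-values alone alter no primary estimate. The article openly concedes low power.

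These arguments limit the point without removing it. The article does prescribe the baseline comparisons. It does set the two analyses side by side, and it names confounding as the reason to adjust. Those are stated choices, and a better one is available from data already collected.

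**Conclusion.** The point holds as a free improvement. The baseline comparisons are uninformative. The two unranked analyses give six primary P-values for three questions, and adjustment rests on the wrong criterion while the stratification factor is not named.

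The size depends on the Holm family. With three members, and with either version allowed to count, family-wise error is about 6.6% to 8.1% against 5%. With six members it is about 3.4% to 4.2%, and the cost falls on power instead. Both ranges assume independent outcomes and covariates explaining 10% to 40% of variance; neither assumption comes from the document. Under either reading the plan does better with one primary analysis per outcome.

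**What to change.** In the Statistical analysis section:

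1. For each primary outcome, name one model as the single primary analysis: the comparison of mean rate of change between arms, adjusted for immunosuppressant stratum and the baseline value of that outcome.
2. State that Holm is applied to those three P-values.
3. Label the unadjusted analysis as a sensitivity analysis.
4. Describe baseline characteristics by arm without significance tests, and state that no covariate will be added because of observed imbalance.

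Stratum is recorded at allocation and the primary outcomes are measured at baseline, so no new data are needed. The cost is a change of wording, and the baseline testing is saved.

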### Visit One (baseline data)

The Xanthin study flow is summarized in Figure 1 and the study evaluations are outlined in Table 2. After obtaining informed consent patients will be contacted by telephone by the trial coordinator at which a date and time is agreed for subject to attend an appointment for baseline trial measures. A letter of confirmation of this appointment and a Xanthin Trial pathology request form will be posted. Patients will be asked to attend the pathology laboratory at least seven days before their first trial visit to have a fasting blood sample collected. At the first trial visit, additional data will be obtained from the medical records (medical history, medications) and measures of height, weight and blood pressure will be recorded. PWV, PWA, CIMT and BAR measures will then be made. At the completion of baseline data acquisition, the trial coordinator explains and asks the subject to take home two questionnaires (SF 36 and items from Active Australia) and a four-day diet diary for completion. The subject is supplied with a self-addressed express post envelope. Subjects are asked to complete and post these tasks within the following two weeks. Subjects are informed that visit two will be approximately six months after visit one. At the completion of visit one, the clinical trial coordinator will provide patients with a three months supply of trial medication as described in the section on randomization. Subjects will be instructed to take three tablets each day preferably with food. The same instructions are provided on the medication container. Finally, participants are provided with a pathology request form for collection of immunosuppressant levels post one-week initial consumption of trial medication (to assess if there is any change to the plasma immunosuppressive levels). Data obtained at the scheduled study visits and are transcribed onto case record forms for entry into a specifically designed Xanthin trial database. Subjects are contacted by telephone ten weeks after visit one, to ascertain their progress with trial medication adherence. The next three months of trial medications will be supplied to them by post. Subjects are then reminded that they will be contacted by telephone in two months time to confirm an appointment date and time for visit two.

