### Withdrawal from Study

Subjects will be withdrawn from the study at their request, without prejudice, as documented and explained at the time of consenting. Patients who withdraw will be asked to consent to follow-up testing for the remainder of the trial to enable an intention to treat data analysis.

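### Per-patient slopes with no stated weighting lose precision, and some patients, whenever the month-12 measurement is missing; a baseline-adjusted mixed model is a cheap improvement

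*Protocol article*

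**What the plan says.** The Abstract sets the schedule: "Patients will undergo these measures at baseline, six and 12 months". The Statistical analysis section fixes a two-stage method. First, "The rates of change will be estimated for each patient separately by linear regression". Then, "General linear modelling, will be used to compare the mean rate of change in primary outcome measures between groups", both unadjusted and adjusted for confounders. It adds that "Mean differences, 95% confidence intervals and P-values will be corrected for repeated measures", without saying what form the correction takes, and applies the Holm method for multiplicity. No weighting of the slopes is stated.

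Under Withdrawal from Study, "Patients who withdraw will be asked to consent to follow-up testing for the remainder of the trial to enable an intention to treat data analysis". The Power calculation section states a 20% withdrawal rate and power of about 17% and 52% for changes of 10% and 20% in pentraxin 3.

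**The concern.** A slope from three visits and a slope from two visits half a year apart are not equally precise. If both enter an ordinary general linear model as single observations, the noisy ones inflate the variance of the treatment comparison. They also project a six-month change to a full year, which is right only if the effect keeps growing linearly. A patient with no post-baseline value cannot enter at all.

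Once each patient is reduced to one slope per outcome, there is one observation per patient, so the promised correction for repeated measures has no clear meaning.

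The protocol admits that its power is small and wants the study to inform a larger one. Precision lost through the choice of estimator is avoidable, and an overstated effect would carry over into the next trial's design.

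**Working it through.** **Inputs from the protocol.** Visits at 0, 0.5 and 1 year. 66 patients, taken as 33 per arm (equal allocation is assumed). Pentraxin 3 mean 0.75, SD 0.3, so a 20% change is 0.15. Alpha 0.05, taken as two-sided.

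**Assumptions not in the protocol.** Correlation 0.5 between any two visits; no true variation in slopes in the base case; several values for the share q lacking month 12. Holm is ignored.

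**Plan's own figure.** A two-sample comparison with 33 per arm and SD 0.3 gives 17.2% and 52.8% (normal) or 17.0% and 51.6% (t) for differences of 0.075 and 0.15. The stated 17% and 52% are reproduced with all 66 analysed. At correlation 0.5 the SD of a change, √(2 × 0.09 × 0.5) = 0.3, equals the SD of a single value, so the 53% below with nobody missing is the same quantity.

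**Slope weights.** The least-squares weights are (tᵢ − t̄)/Sxx and the error variance is σ²/Sxx.
- 0, 0.5, 1: weights (−1, 0, +1); slope y12 − y0; error variance 2σ².
- 0, 0.5: weights (−2, +2); slope 2(y6 − y0); error variance 8σ², four times larger.
- 0 only: Sxx = 0; no slope.

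The six-month visit is only approximately timed. At 5 or 7 months its weight in a completer is −0.11 or +0.11.

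**Power for a 0.15 difference.** σ² = 0.09 × 0.5 = 0.045, so a completer's slope has variance 0.09 and a 0/6-month slope 0.36. With q = 0.2:
- Unweighted slopes: (2/33) × (0.8 × 0.09 + 0.2 × 0.36) = 0.00873; SE 0.0934; power Φ(0.15/0.0934 − 1.96) ≈ 36%.
- Completers only: (2/33) × 0.09/0.8 = 0.00682; SE 0.0826; power about 44%.
- Weighted slopes: (2/33)/(0.8/0.09 + 0.2/0.36) = 0.00642; SE 0.0801; power about 47%.
- Baseline-constrained longitudinal model (covariance treated as known): variance 0.0050; SE 0.0707; power about 56%.

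| Share lacking month 12 | Unweighted slopes | Weighted slopes | Baseline-constrained model |
|---|---|---|---|
| 0% | 53% | 53% | 65% |
| 5% | 47% | 51% | 63% |
| 10% | 43% | 50% | 61% |
| 20% | 36% | 47% | 56% |

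**Where the gain comes from.** At 20% missing, a longitudinal model without baseline adjustment reaches 47%. Of the rise from 36% to 56%, about 11 points come from handling unequal precision and about 9 from baseline adjustment. With nobody missing, all of the gain (53% to 65%) is baseline adjustment.

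**If true slopes vary.** With slope variance τ², the total variance ratio of a 0/6-month slope to a completer's is (τ² + 8σ²)/(τ² + 2σ²): 4 at τ² = 0, 3 at τ² = σ², 2 at τ² = 4σ². The variance of the unweighted mean slope relative to the weighted one is then 1.36, 1.21 and 1.08 with 20% missing, and 1.20, 1.12 and 1.05 with 10% missing.

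**Plateau.** If the whole 0.15 effect is present at six months and stays there, a 0/6-month patient contributes 0.30. With 20% such patients the expected estimate is 0.8 × 0.15 + 0.2 × 0.30 = 0.18, which is 20% too large. With 5% it is 0.95 × 0.15 + 0.05 × 0.30 = 0.1575, or 5% too large.

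**The case against.** Two-stage slopes are a recognised and valid method, and they match the protocol's hypothesis, which concerns rates of change. That stands: the method is not invalid, and with every month-12 value in hand it is identical to a longitudinal comparison without baseline adjustment.

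The absence of weights is inferred from silence, and the adjusted analysis might include baseline. That also stands in part. Equal weighting is the default reading of a general linear model on patient slopes, and the undefined repeated-measures correction does not clearly change it, but the text does not say so outright.

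Three stronger readings are tempting and should not be drawn.

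- *That separate slopes waste the six-month visit in completers.* The zero weight comes from a linear trend on three equally spaced visits. A mixed-model slope gives the same weight, and so does the 12-month contrast recommended below when the correlation between visits is constant.
- *That the intention-to-treat analysis is abandoned.* The protocol asks withdrawers to consent to continued testing, "to enable an intention to treat data analysis", and those who agree supply a full slope. The shortfall is confined to those who do not, and their number is unknown.
- *That the planned estimator is worse than discarding incomplete patients, or that it overstates the effect by 20%.* Both need all of the 20% withdrawal to fall after month 6 with no month-12 test. The first also needs little slope heterogeneity: at τ² = 4σ² the unweighted slopes do slightly better than discarding. The second needs a complete plateau by six months. The documents establish none of this.

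Detailed missing-data rules may well sit in a fuller plan. The point here is the estimator that the article does fix.

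**Conclusion.** The point holds in a limited form. The stated analysis is sound when follow-up is complete, apart from the precision that baseline adjustment would add. When month 12 is missing it gives noisier slopes equal weight on the default reading, doubles a plateaued effect in those patients and excludes anyone with only a baseline. The repeated-measures clause is unclear alongside it.

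Under the illustrative assumptions, the loss against weighted slopes is about 4 percentage points of power with 5% lacking month 12, 7 with 10% and 11 with 20%. It shrinks as true slopes vary more. Baseline adjustment adds a further 9 to 12 points at correlation 0.5, whether or not data are missing. The correlation, the slope variance and the share lacking month 12 are assumptions, so the figures show scale and do not forecast this trial's power. This is a worthwhile improvement in method, not an error that invalidates the trial.

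**What to change.** For each primary outcome, fit one likelihood-based mixed model to all available visits, with categorical visit, treatment-by-visit, a baseline mean common to both arms (or baseline as a covariate) and immunosuppressant stratum. Make the 12-month treatment difference the primary contrast; in completers this is the quantity the slope already estimates. Include every randomised patient with data. The common-mean form keeps baseline-only patients in the model, though they carry no direct information on change. Delete the repeated-measures clause or define what it means.

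If a rate of change must remain the target, use precision-weighted slopes or a random-slope mixed model, adjusted for baseline.

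The cost is analysis wording only, with no new data or visits. The one downside is that the result is reported as a 12-month difference and not as a slope. The change should not be presented as giving month 6 more weight in completers; its value there is a separate six-month contrast and information for patients whose month-12 value is missing.

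### The comparison of slopes is planned unadjusted and adjusted for confounders, with neither version primary and no commitment to the stratification factor or the baseline value

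*Protocol article*

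**What the plan says.** Under Randomization the protocol article states: "Subjects will also be stratified according to four groups according to the type of immunosuppression used". Each stratum has its own blocks of ten.

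Under Statistical analysis, a linear regression is fitted to each patient's values, and the mean slopes are compared between arms by a general linear model, "unadjusted and adjusted for actual and potential confounding variables". No covariate is named. The text does not say whether the unadjusted or the adjusted comparison is the primary one, although Holm-corrected P-values are to be reported. The same section begins with tests of baseline variables between the groups.

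The fourth stratum is described in two ways. The abstract (Method and Design) has "prednisolone+/-azathioprine, mycophenolate mofetil or mycophenolate sodium", while Randomization has "prednisolone together with either azathioprine, mycophenolate mofetil or mycophenolate sodium".

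**The concern.** A factor used to balance the allocation, and the baseline value of the outcome, belong in the model of a randomised trial because one was used in the design and the other is prognostic. Both are known in advance. The article chooses covariates by confounding instead, which is not the right criterion once treatment is randomised. If actual confounders means those found imbalanced (a possible reading; the text does not define the term), the rule would tend to pass over the stratum, because stratification balances it.

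Two things are at stake. First, with two models and no stated primary, the Holm-corrected P-values have no unique source. Second, precision may be lost in a trial whose own Power calculation section concedes low power, although the relevant data are already collected.

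**Working it through.** **Inputs from the Power calculation section.** "Resource limitations will allow us to recruit 66 patients within a two-year period". The pentraxin 3 figures are "pentraxin 3 = 0.75 ± 0.3", so a 10% change is 0.075 and a 20% change is 0.15. Alpha is 0.05. I assume two-sided testing and 1:1 allocation, 33 per arm; neither is stated.

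**The plan's own figure.** The article says: "with alpha = 0.05, we will have about a 17% power to detect this 10% change in pentraxin 3", and gives 52% for a 20% change. A two-sample comparison with SD 0.3 and 33 per arm gives 17.0% and 51.6% by noncentral t (17.2% and 52.8% by normal approximation). The figures therefore reproduce, with all 66 patients and no credit for covariates. With 26.4 per arm (20% withdrawn) the t-test result would be 14.5% and 43.0%. The comparisons below stay at 33 per arm to match the stated power.

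**The slope in completers.** With visits at 0, 0.5 and 1 year, the least-squares weights are (x − mean) / Σ(x − mean)² = −0.5/0.5, 0/0.5, 0.5/0.5 = −1, 0, +1. The slope per year is the 12-month value minus baseline; the 6-month value has no weight. The unadjusted comparison is therefore a change-score analysis.

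**Gain from conditioning on baseline.** With equal variances s² and correlation rho between baseline and 12 months:
- change score: variance 2s²(1 − rho)
- baseline-adjusted: variance s²(1 − rho²)
- ratio: (1 − rho²) / [2(1 − rho)] = (1 + rho)/2

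The documents give no rho, so a range is shown, with s = 0.3:

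| rho (assumed) | SD, slope | SD, baseline-adjusted | Variance ratio | Power, 10% change (normal) | Power, 20% change (normal) | Power, 20% change (t) |
|---|---|---|---|---|---|---|
| 0.3 | 0.355 | 0.286 | 0.65 | 13.5% → 18.5% | 40.4% → 56.7% | – |
| 0.5 | 0.300 | 0.260 | 0.75 | 17.2% → 21.6% | 52.8% → 65.0% | 51.6% → 63.7% |
| 0.7 | 0.232 | 0.214 | 0.85 | 25.8% → 29.5% | 74.6% → 81.2% | 73.3% → 80.0% |
| 0.9 | 0.134 | 0.131 | 0.95 | 62.2% → 64.4% | 99.5% → 99.7% | – |

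At rho 0.5 the SD of the change equals the SD of a single value, so the article's 52% is also the change-score power at that correlation. With 26.4 per arm the gain for a 20% change is similar: 44.3% to 55.5% at rho 0.5 and 65.0% to 72.0% at rho 0.7 (normal).

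**Effect of leaving out the stratum.** If the stratum explains a share R2 of the variance of the slope, the unadjusted standard error is too large by 1/√(1 − R2), and the actual two-sided error rate is about 2Φ(−1.96/√(1 − R2)). R2 is not in the documents.

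| R2 (assumed) | SE too large by | Actual type I error |
|---|---|---|
| 0 | 0% | 5.0% |
| 0.05 | 2.6% | 4.4% |
| 0.10 | 5.4% | 3.9% |
| 0.20 | 11.8% | 2.8% |

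In power terms, if the slope's SD is 0.3, an R2 of 0.10 would move a 20% change from 52.8% to 57.2% (normal).

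**Stratum 4.** The abstract's plus-or-minus sign admits prednisolone alone. The Randomization text requires a second agent. A patient on prednisolone alone is in stratum 4 under one definition and in no stratum under the other.

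**The case against.** A reader might infer that the primary model leaves out both the stratum and the baseline value. The text does not support this: no model is called primary, and the adjusted version has an open list that could include both. What stands is that the plan commits to neither.

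The article is condensed, and a covariate list is commonly left to an analysis plan that is not shown. That is fair as far as the list goes. But the article does state a rule for choosing covariates and sets two versions side by side without ranking them; those are choices made in the text.

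The slope already uses the baseline value, removes the patient's level, and matches the hypotheses, which are framed as rates of change. This is correct, and the slope comparison is valid. What is forgone is only the further gain from conditioning on baseline. Nor can that gain be called precision already bought by the design, since stratification covers immunosuppressant only.

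The stratum may matter little. The Background reports that cyclosporine raises oxidative stress markers and lowers vascular function, but it does not say that the four regimens differ in one-year change. A stable difference in level cancels from the slope, leaving R2 near zero. This stands, so the range must include zero.

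Finally, a reader might fear bias or too many false positives. Neither follows: any error in the standard error from omitting the stratum is in the conservative direction.

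**Conclusion.** The point holds as one of efficiency and of an unfixed primary analysis. Baseline adjustment is the larger potential gain: about 12 percentage points of power for a 20% change in pentraxin 3 at rho 0.5, about 7 at rho 0.7, and almost nothing at rho 0.9. These figures assume equal variances at the two visits, 33 per arm, complete follow-up and a correlation that the documents do not give. The stratum's contribution lies between nothing and a modest amount, depending on an unknown R2 for the slope. The change is worth making because it costs almost nothing and also settles which P-values enter the Holm procedure.

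**What to change.** For each of the three primary outcomes, prespecify one primary model with treatment, immunosuppressant stratum as randomised, and the baseline value of that outcome. Apply the Holm correction to the treatment P-values from these three models. Report the unadjusted comparison of slopes as a sensitivity analysis, and drop confounding as the criterion for choosing covariates.

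Before the stratum is used as a model term, reconcile the abstract and the Randomization section on whether prednisolone alone belongs to the fourth group, and state the definition actually used at allocation.

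The cost is a change of wording and about four degrees of freedom (three for the stratum, one for baseline) out of 66 patients. No new data are needed: the immunosuppressant type is recorded at allocation and each primary outcome is measured at baseline.
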